## Methods/design

### Design

Sixty depressed Latinos with LEP from the community will be randomized to receive individual BATD (*n* = 30) or an individual contact time-matched SC condition (*n* = 30). The design allows for the examination of treatment group differences in depression, activity level and contact with environmental reinforcement, treatment adherence, treatment satisfaction, therapeutic alliance, and perceived stigma between conditions, consistent with our three study aims. Assessments take place immediately prior to each session and at 1-month post-treatment. This study was approved by the University of Maryland-College Park’s Institutional Review Board (protocol no. 403879–2). We requested to obtain participants’ verbal informed consent and not written informed consent to protect the privacy and confidentiality of a sample that may be represented predominantly by immigrant Latinos, who may not be in the US on legal terms.

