Participants earn $15 for the completion of questionnaires at the baseline assessment and the post-treatment assessment (corresponding to sessions 1 and 10 of treatment). Participants are paid $10 for the remaining scheduled assessment points. Participants are assessed prior to each treatment session. In the situation that participants do not qualify during the baseline interview, they are paid for completing the baseline assessments. In general, the completion of the assessments during the first and last meetings take up to 70 minutes, and up to 20 minutes for the remaining meetings. After completing the assessments, participants receive compensation.At the first meeting, a staff member not involved in the study conducts the randomization using a computerized random number generator and informs the participant’s therapist of the assigned therapy condition in person. The research assistant conducting assessments for a participant is blind to every participants’ assigned treatment condition. Blinding is facilitated by the fact that participants complete identical assessment measures regardless of their assigned condition throughout the course of the study. This removes any need for research assistants to be informed about participants’ randomization outcome. Therapy commences thereafter, and therapy sessions last approximately 60 minutes. Figure 2 provides a flow diagram of study procedures from recruitment to randomization.

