SC does not follow a specific theoretical model and is best described as offering the client unconditional support. The discussion for each session is patient-driven, and the manual includes training in therapy using SC techniques including reflections, empathic listening, encouragement, and help in exploration and expression of feelings and experiences, without advice giving, solution offering or skills teaching. Each SC session concludes with a scripted relaxation exercise. The manual is organized in a way that reviews the basis for supportive psychotherapy, the meaning of establishing a supportive relationship, steps for beginning the therapy session, session management, crisis management, and ethical factors in supportive psychotherapy. Therapists are trained in these procedures, in using non-directive techniques and in avoiding BATD techniques. These topics are covered in different chapters within the manual.

The SC condition also includes journal writing homework forms. The amount of homework assigned in the SC condition is matched with BATD. Participants are asked to write in the journal forms once a day about any topic that they would like.

#### **
*Assessments*
**

In line with our study aims, participants complete questionnaires to assess five principal domains. Table 1 offers a summary of the questionnaires, the domain they assess, and the time-point at which they are administered.

**Table 1 T1:** Schedule of questionnaire administration

**Assessment**	**Baseline/Session 1**	**Session 2**	**Session 3**	**Session 4**	**Session 5**	**Session 6**	**Session 7**	**Session 8**	**Session 9**	**Session 10**	**1-month post-treatment**
Domain 1: participant characteristics											
Demographics	X										
Acculturative stress	X										
Other medication/treatment use	X									X	X
Domain 2: depressive symptomatology											
SCID-IV modules	X									X	X
Beck Depression Inventory-II	X	X	X	X	X	X	X	X	X	X	X
Hamilton Rating Scale for Depression	X	X	X	X	X	X	X	X	X	X	X
Domain 3: behavioral activation and reinforcement derived from the environment											
Behavioral Activation for Depression Scale	X	X	X	X	X	X	X	X	X	X	X
Reward probability index	X	X	X	X	X	X	X	X	X	X	X
Domain 5: attitudes toward treatment											
Stigma checklist	X				X					X	X
Therapeutic alliance	X				X					X	X
Treatment satisfaction	X				X					X	X

SCID-IV, Structured Clinical Interview for the Diagnostic Statistical Manual version IV text revision.

##### 

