**Domain 5 - treatment correlates** To measure stigma-related concerns associated with receiving treatment for depression, participants complete the Stigma Checklist Questionnaire [62], a measure specifically designed for use with low-income Spanish-speaking or bilingual Latino patients. The questionnaire consists of 7 items designed to identify participants’ perceptions of others who have depression and take medication, as well as their fear of relatives learning that they are dealing with depression. The reliability of the scale has been reported at a Cronbach’s alpha of 0.69.

The Therapeutic Alliance with Clinician Questionnaire [63] assesses the strength of the therapeutic relationship using a 9-item Likert scale format. The Spanish version of the questionnaire [64] was evaluated with a sample predominantly comprised of depressed individuals and achieved high internal consistency (*α* = 0.96) and an item component correlation of 0.70. The authors concluded that the measure has both clinical and research utility.

To elicit feedback about both treatment conditions, we administer an in-house developed questionnaire every other session. Participants rate the treatments on a 0 to 5 Likert-type scale across 10 items including “to what extent do you believe that this treatment has improved your depression/low mood?”, and “how valuable do you think this treatment would be for individuals who experience depressed/low mood?” This treatment satisfaction scale ranges from 0 to 50, with higher scores representing higher satisfaction.

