
To examine more closely the effects of treatment on attendance, we will conduct a Cox proportional hazards survival analysis predicting days to attrition. This will allow us to examine the extent to which BATD was able to increase the latency to treatment attrition. Homework completion will be assessed by dividing the total number of completed homework sessions by the total number of assigned homework sessions for each participant. We will conduct *t*-tests to examine differences in homework completion between BATD and SC.

Finally, we will conduct *t*-tests examining differences between BATD and SC in treatment satisfaction, therapeutic alliance, and perceived stigma at each session these correlates were examined.

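### The Aim 3 t-tests at each of four occasions include session-1 readings taken before any therapy, name no key time point, and rest on a satisfaction schedule that the article contradicts

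*Protocol article*

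**What the plan says.** The Data analysis plan ends with the Aim 3 comparison of the three treatment correlates: t-tests "examining differences between BATD and SC in treatment satisfaction, therapeutic alliance, and perceived stigma at each session these correlates were examined". When the measures are taken is set out under Assessments, where "Table 1 offers a summary of the questionnaires, the domain they assess, and the time-point at which they are administered". Under the row heading "Domain 5: attitudes toward treatment", Table 1 marks stigma, alliance and satisfaction at Baseline/Session 1, Session 5, Session 10 and 1-month post-treatment. For satisfaction, however, the Domain 5 text says that "we administer an in-house developed questionnaire every other session".

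On timing, the Design section states: "Assessments take place immediately prior to each session and at 1-month post-treatment". Procedure and randomization describes the first-meeting assessments and randomization, then says: "Therapy commences thereafter, and therapy sessions last approximately 60 minutes". The same section notes that participants are told nothing about treatment content beforehand.

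The alliance questionnaire "assesses the strength of the therapeutic relationship using a 9-item Likert scale format". One satisfaction item asks "to what extent do you believe that this treatment has improved your depression/low mood".

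The Background gives a directional hypothesis for each measure but names no time point. It also says that these variables affect retention, and it expects better retention under BATD. The Discussion anticipates that dropout may be high. Hierarchical linear modelling, chosen partly because it tolerates missing readings and allows control for baseline scores, is assigned to the first and second aims only.

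**The concern.** The testing rule is tied to whenever the measures were taken, and that has four consequences.

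- It takes in readings made before the participant has had any therapy. A difference between arms at that point can only be chance or a reaction to something other than treatment.
- The number of tests depends on a schedule that the article states in two ways.
- With four occasions per measure and none singled out, a difference at any one of them could be offered as support for the hypothesis.
- A cross-sectional t-test uses only those who supply a reading on that day. The article's own premises are that these attitudes influence who stays and that staying will differ by arm.

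At stake is the interpretation of Aim 3, not the primary depression comparison.

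**Working it through.** The article states no error rate, power or sample size for Aim 3, so there is no figure to reproduce.

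**1. Timing.** Set side by side:
- Table 1 places alliance and satisfaction at Baseline/Session 1.
- The Design section puts assessments before the session.
- Procedure and randomization puts therapy after the first-meeting assessments and randomization.

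At the session-1 reading there is thus no therapeutic relationship to rate and no treatment that could have improved mood. Stigma can be measured then, but a between-arm test of it is a check of baseline balance. So 3 of the 12 planned tests cannot show a treatment effect.

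**2. Number of tests.**
- Table 1: 3 measures × 4 occasions = 12.
- If the 1-month visit is not counted as a session: 3 × 3 = 9.
- Satisfaction every other session, read (an assumption) as 5 in-treatment occasions without or with the 1-month visit: 4 + 4 + 5 = 13 or 4 + 4 + 6 = 14.

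**3. Family-wise error.** For k independent tests at 0.05 the chance of at least one false positive is 1 − 0.95^k. The correlated figures come from a simulation under no true effect (30 per arm, 20,000 runs). It assumed correlations of 0.3–0.8 between occasions and 0.2–0.5 between measures.

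| Tests | Independent | Assumed correlations |
|---|---|---|
| 12 (all) | 1 − 0.95^12 = 46.0% | 27–43% |
| 10 (session-1 alliance and satisfaction removed) | 1 − 0.95^10 = 40.1% | not run |
| 9 (all session-1 tests removed) | 1 − 0.95^9 = 37.0% | 24–35% |
| 3 (one time point per measure) | 1 − 0.95^3 = 14.3% | 13–14% |

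Each single test stays near 5%. Removing the pre-treatment comparisons lowers the family-wise figure only a little; naming one time point lowers it much more.

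**4. Readings from attenders only.** The article does not say that Aim 3 is restricted to attenders. It follows from the timing: a questionnaire given just before session 5 or 10 is not completed by someone who has stopped coming.

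The article gives no dropout rate, so these values are assumed: no true difference, dropout of 20% in BATD and 40% in SC, and a correlation of 0.5 between the score and the tendency to stay. The mean score among stayers, in SD units, is r × φ(z_p)/(1 − p), where p is the dropout proportion:
- BATD: 0.5 × 0.280/0.8 = 0.175
- SC: 0.5 × 0.386/0.6 = 0.322
- Difference: 0.175 − 0.322 = −0.147 SD, against BATD.

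Simulation over a range of assumptions (6,000 runs each):

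| Dropout BATD / SC | Correlation | Bias (SD) | Error of one test |
|---|---|---|---|
| 20% / 20% | 0.3–0.6 | about 0 | about 5% |
| 20% / 40% | 0.3 | −0.08 | 6% |
| 20% / 40% | 0.6 | −0.18 | 9% |
| 20% / 50% | 0.3 | −0.13 | 7% |
| 20% / 50% | 0.6 | −0.26 | 14% |

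With zero correlation the bias is also about 0.

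**5. Baseline stigma as a covariate.** The residual variance is multiplied by 1 − r². At an assumed baseline-to-later correlation of 0.5 the reduction is 25%; at 0.3 it is 9%, and at 0.7 it is 49%.

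**The case against.** **Multiplicity.** These are third-aim correlates, and the article is silent on adjustment rather than ruling it out. A rule may sit in an analysis plan that is not shown. That stands: the lack of a stated adjustment is not an error in itself. Testing at every measured occasion is nevertheless the article's own choice. A reader might also infer that some chance finding is likely. The figures do not support that: even under independence the probability is 46%, and correlation lowers it.

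**Attendance.** A reader might infer that all the Aim 3 comparisons are confined to those who stay. They are not. Session 1 is unaffected, and the article does not say whether people who leave treatment are still assessed at 1 month. Patterns of missing data and dropout are to be examined first, though no method for handling them is tied to these t-tests. The illustrated bias runs against BATD, so in that scenario it would not create support for the satisfaction and alliance hypotheses; it could hide a real benefit.

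**Session-1 satisfaction.** A forward-looking item on how valuable the treatment would be could be read as expectancy. The improvement item and the alliance scale cannot be read that way.

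**Baseline stigma.** It would be wrong to say that this reading goes unused, since the rule tests it at session 1. It is only not named as a covariate. The t-test stays valid without it, so the argument there is one of precision.

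**The remedy.** A mixed model does not remove the attrition problem. That stands, and the cost is stated with the fix.

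**Conclusion.** The point holds in a limited form. Two parts follow from the text without outside assumptions. The testing rule includes session-1 alliance and satisfaction comparisons that cannot reflect treatment, plus a stigma comparison that is only a balance check. The satisfaction schedule is also given in two incompatible ways, which leaves the number of tests unsettled.

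Two parts are conditional. The family-wise error is 46% if the 12 tests are independent and about 27–43% under the assumed correlations. The bias at sessions 5 and 10 requires dropout that is related to the score and differs by arm. It is about 0.15 SD in the illustration and 0.08–0.26 SD over the simulated scenarios with unequal, score-related dropout.

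The wording should not be read as testing at every treatment session: Table 1 marks 4 of its 11 occasions. The matter concerns a secondary aim and is worth correcting, but it does not undermine the primary comparison.

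**What to change.** 1. Exclude the session-1 alliance and satisfaction readings from treatment comparisons.
2. For each measure, replace the separate t-tests with one mixed model over session 5, session 10 and 1 month. Include everyone with at least one of those readings, and pre-state one contrast, for example the treatment difference at session 10.
3. Use baseline stigma as a covariate in the stigma model instead of testing it between arms.
4. Label the three Aim 3 contrasts exploratory, or adjust them, for example by Holm (the strictest step is 0.05/3 = 0.0167).
5. Reconcile the Domain 5 text with Table 1 on when satisfaction is collected. Recruitment is under way, so state which schedule has been followed.

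The cost is some wording, one corrected table or sentence, and slightly more analysis work with a method already planned for Aims 1 and 2. The limit is that the model reduces attrition bias only as far as observed data explain dropout. It cannot recover people who have no reading after session 1, so their number should be reported by arm.

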Following up this promising initial work, the current study is comprised of an RCT with three aims. First, we will compare the impact of BATD and a supportive counseling (SC) condition on participants’ depression throughout the course of the study. We expect that participants randomized to BATD will evidence greater reductions in depressive symptoms and a higher percentage remission of MDD relative to participants randomized to the SC condition. Second, we will compare group differences on the proposed mediators of BATD, including activation and contact with environmental reward. We hypothesize that participants assigned to the BATD condition will evidence greater increases in activation and contact with environmental reward relative to those assigned to the SC condition. We also expect that increases in activation and contact with environmental reinforcement will correspond with decreases in depression. Figure 1 is a depiction of the models tested under this aim. Third, we will examine SC and BATD group differences on key conceptually relevant variables associated with treatment retention and outcomes in Latinos, such as treatment satisfaction [41], therapeutic alliance [42], and perceived stigma [43], as these variables have been shown to affect treatment outcomes and retention in this population. In the context of the third aim, we will compare dropout rates between conditions. We expect that, relative to participants assigned to the SC condition, participants randomized to BATD will evidence higher treatment satisfaction given the heavy emphasis of BATD on putting effort into one’s recovery from depression ("poner de su parte"), a treatment expectation highly valued in this population [44,22]. Further, we hypothesize greater therapeutic alliance in the BATD condition given the collaborative approach expected to emerge between the client and the therapist in this treatment condition [45]. We also hypothesize that, as a result of the conceptualization of depression of BATD as originating from the lack of environmental reinforcement, perceived stigma levels will be lower relative to the SC condition. Finally, we expect that treatment retention will be greater for the BATD condition than for the SC condition based on previous findings suggesting this trend [39,40].

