### Sample size considerations

We based our sample size needs on effects observed in the literature, including other treatment studies, and by making informed decisions about the magnitude of effects of BATD in this population that would likely be of clinical significance. For the primary hypothesis that BATD would result in greater reductions in depressive symptoms, we calculated the sample size required based on a recent meta-analysis conducted that examined the effect size of BA relative to control conditions [29] and on a treatment study that compared cognitive behavioral therapy to an active treatment condition (interpersonal psychotherapy) conducted by Rosselló and colleagues [65] in a Spanish-speaking Latino sample. These studies yielded effect sizes of 0.43 and 0.74, respectively, indicating medium to large effects. Our proposed sample size of 30 in each cell fits well within that suggested by a power analysis using these two reported effect sizes to allow for a power of 0.80 using an alpha of 0.05 [66]. Our sample size also follows recommendations of including 15 to 30 subjects per cell in this stage of treatment development [67].

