### Data analysis plan

We will first assess equivalence of random assignment of groups, patterns of missing data, research dropout rates, and distributional properties of all measures. Hierarchical linear modeling (HLM) [68] will be used to examine within-subject change of depression (first aim) and activation and reinforcement derived from the environment (second aim) over the course of treatment. The nature of HLM analyses allows us to control for baseline scores of each measure, include multiple measurement points while accommodating missing data, examine individual change over time in outcomes, and include the average change and the individual variation around this average change. We will specify all of our HLM level-1 intercepts and slopes as random, given that we expect first session depressive symptomatology, activation, and availability of reinforcement in the environment, as well as each individual’s slope of these constructs, to differ across our participants. We will center all variables of interest around the mean of respective scores to avoid multicollinearity. Planned covariates in these analyses will include gender, recruitment method, and baseline levels of depressive symptoms, as well as the main effect of treatment condition and the linear effect of time. Inclusion of the time by treatment condition interaction will indicate the extent to which treatment differences are more or less pronounced early versus later across treatment sessions. Categorical rates of remission of MDD will be examined across treatment conditions using the Cochran-Mantel-Haenszel test, controlling for gender.To examine the correspondence between increases in activation and environmental reinforcement with depression, we will also use HLM to examine correspondence of these variables over time. These models will include the aforementioned covariates in addition to including activation and environmental reinforcement as time-varying predictors of depression, the main effect of treatment condition, the linear effect of time, and the inclusion of time by treatment condition interaction. Because of the difficulty in attributing causality between variables assessed at the same time-point, we will also conduct analyses predicting depression with environmental reinforcement and activation assessed at the previous time-point as time-varying covariates (please see Figure 1 depicting the lagged and concurrent analyses). These lagged analyses will indicate whether the predictors predict change in depression at subsequent assessments, consistent with the BATD framework that activation and environmental reinforcement are expected to increase before depression decreases.

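### Perceived stigma is compared by unadjusted t-tests although a pre-therapy stigma score is collected: valid on average, but precision is given up for no saving

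*Protocol article*

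**What the plan says.** The aims paragraph of the Background makes a directional prediction for BATD: "perceived stigma levels will be lower relative to the SC condition". The last paragraph of the Data analysis plan fixes the test as t-tests "examining differences between BATD and SC in treatment satisfaction, therapeutic alliance, and perceived stigma at each session these correlates were examined". It names no covariate, change score or longitudinal model for these outcomes.

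Table 1 (under Assessments) has a row "Stigma checklist", marked at baseline/session 1, session 5, session 10 and 1 month after treatment. The Design section says "Assessments take place immediately prior to each session and at 1-month post-treatment". Procedure and randomization describes the first-meeting assessments and the randomization, then adds "Therapy commences thereafter, and therapy sessions last approximately 60 minutes". The session-1 stigma score is therefore a pre-therapy measurement.

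Elsewhere the plan does value baseline control: "The nature of HLM analyses allows us to control for baseline scores of each measure". That sentence, and the covariate list after it, belong to the hierarchical models for depression (first aim) and for activation and reinforcement (second aim). Stigma is not among them.

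**The concern.** A participant's stigma at session 10 probably depends in part on his or her stigma at entry. Comparing raw follow-up scores leaves that between-person variation in the error term, although the measurement that would remove part of it has been collected. Perceived stigma differs here from alliance and satisfaction. The checklist asks about views of people with depression and fear of relatives finding out, which is meaningful before therapy starts.

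The stigma hypothesis is tested with 30 per arm at most, and the Discussion concedes that real differences may be missed in so small a sample. A less precise test adds to that weakness. In addition, if the arms happen to differ in stigma at entry, part of that difference reappears in each follow-up contrast, and nothing in the plan removes it.

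Read literally, the plan also applies a t-test to session 1. That comparison precedes therapy and says nothing about the hypothesis.

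**Working it through.** **Inputs from the article.** 30 per arm, power 0.80, alpha 0.05, effect sizes 0.43 and 0.74 (Sample size considerations). These effect sizes are for depressive symptoms; none is given for stigma. The stigma scale's Cronbach's alpha is 0.69 (Domain 5).

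**Assumptions.** Two-sided testing, since sidedness is not stated. A correlation rho between session-1 and later stigma, which the article does not give; 0.3 and 0.5 are used, with 0.7 as an outer value. No dropout.

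**Step 1: the plan's own figure.** The article states "Our proposed sample size of 30 in each cell fits well within that suggested by a power analysis". A two-sample t-test at d = 0.74 with power 0.80 needs 29.7, so 30 per arm, and power at 30 per arm is 0.805. The figure reproduces at 0.74. It does not at 0.43, where 86 per arm are needed and power at 30 is 0.37. That concerns depression; here it only confirms that the power calculation is set up as the plan intends.

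**Step 2: what adjustment gains.** With baseline as covariate the residual SD is SD × √(1 − rho²), so the t-test power is evaluated at d/√(1 − rho²). The one lost degree of freedom is ignored.

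| rho | variance removed (rho²) | equivalent unadjusted n per arm, 30/(1 − rho²) | power, d = 0.43 | power, d = 0.74 |
|---|---|---|---|---|
| 0 (t-test) | 0% | 30 | 0.37 | 0.80 |
| 0.3 | 9% | 33 | 0.40 | 0.84 |
| 0.5 | 25% | 40 | 0.47 | 0.90 |
| 0.7 | 49% | 59 | 0.63 | 0.98 |

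A simulation of 20,000 trials with 30 per arm agrees: at d = 0.74, ANCOVA power was 0.83 (rho 0.3) and 0.90 (rho 0.5), against 0.80 to 0.81 for the t-test.

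The difference detectable with 80% power (normal approximation) is (1.96 + 0.8416) × √(2/30) × √(1 − rho²). This is 0.72 SD unadjusted, 0.69 SD at rho 0.3 and 0.63 SD at rho 0.5.

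**Step 3: which rho is plausible.** If alpha 0.69 is taken as a rough reliability at both occasions, an observed rho of 0.3 needs a true-score correlation of 0.3/0.69 = 0.43, and 0.5 needs 0.5/0.69 = 0.72. For 0.7 the ratio exceeds 1. The last table row is therefore an outer bound, and 0.3 to 0.5 is the sensible range to read.

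**Step 4: chance imbalance.** The standard error of the baseline difference is √(2/30) = 0.26 SD. The probability of a difference of at least 0.30 SD in either direction is about 25%. The t-test carries rho times it: 0.3 × 0.30 = 0.09 SD, or 0.5 × 0.30 = 0.15 SD. Given exactly 0.30 SD, the false-positive risk is 5.3% (rho 0.3) or 5.7% (rho 0.5). Given 0.50 SD it is 8% or 13%; an imbalance that large or larger has probability of about 5% (0.50/0.26 ≈ 1.94 standard errors).

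**Step 5: error averaged over randomizations.** Under no effect, with rho 0.3 to 0.7, simulated type I error was 5.0% to 5.2% for both the t-test and ANCOVA.

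**The case against.** The strongest reply is that both tests are valid. Randomization makes the unadjusted comparison unbiased, and its standard error already allows for chance baseline differences. A reader might infer that the stigma result would be confounded, or that a baseline difference would routinely pass for a treatment effect. The documents do not support that. Overall error stays at 5%, and it is clearly raised only after an imbalance that is itself uncommon. This part of the reply stands in full.

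Second, an imbalance would be visible. The plan says "We will first assess equivalence of random assignment of groups", and a literal reading of the t-test sentence includes session 1. This also stands, but seeing an imbalance neither removes it from later contrasts nor recovers precision.

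Third, the hypothesis is about levels, and a t-test compares levels. So does ANCOVA, with a smaller error term.

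Fourth, the size of the gain rests on quantities that the article does not give for stigma. The effect sizes are borrowed from another outcome and the correlation is assumed. At rho 0.3 the gain is only 3 to 4 power points. At d = 0.43 and rho 0.5 the comparison still has power below one half, so adjustment does not make it adequately powered. These limits stand and are built into the conclusion.

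Finally, a condensed article may leave covariate detail to a fuller plan. Here, however, the test and its occasions are stated, so this is a stated choice and not an omission.

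**Conclusion.** The point holds as one of efficiency. The plan names an unadjusted test for an outcome whose pre-therapy value it already collects, and its baseline control does not reach that outcome. The harm is lost precision, plus a follow-up contrast that carries rho times any realized baseline imbalance. It is not bias on average and not an inflated overall error rate.

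By way of illustration, the gain is 3 to 4 power points at a correlation of 0.3 and about 10 at 0.5. This rests on 30 per arm, two-sided 0.05, no dropout, and effect sizes stated for depression. The scale's reliability makes very high correlations, and so much larger gains, unlikely.

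The point is confined to perceived stigma. A reader might extend it to alliance and satisfaction because Table 1 also lists them at session 1, but before therapy there is no alliance or treatment experience to adjust for. Stigma is an Aim 3 outcome, and the primary depression analysis is untouched. The change is worth making because it costs almost nothing.

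**What to change.** In the last paragraph of the Data analysis plan, take perceived stigma out of the t-test sentence. State that stigma at session 5, session 10 and 1 month will be compared between arms by ANCOVA, or by one repeated-measures model, with the session-1 stigma score as covariate. Report session-1 stigma by arm descriptively, without a test.

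The cost is a sentence of analysis wording and about one degree of freedom; the data are already scheduled. The article gives the trial status as recruiting, so the change can be specified before outcomes are analyzed.
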